## Abstract

Background

Women and adolescent girls with disabilities suffer the most difficulties during menstruation days in developing countries like Bangladesh. They deal with menstruation in a hazardous and unclean manner. In Bangladesh, men serve as the family's gatekeepers for health-seeking behavior. But they frequently have no idea how unpleasant and demanding menstruation can be. Menstrual hygiene care for women and adolescent girls with disabilities can be improved by involving male peers. In Bangladesh, no such intervention has been assessed. The purpose of the study is to assess the effects of male participation on menstrual hygiene management of women and adolescent girls with disabilities in Bangladesh.

Methods

This will be a quasi-experimental study with a sample size of 120 (60 - control, 60 - intervention). The study will be conducted in a sub-district of Bogura and Chapainawabganj in Bangladesh. Inclusion criteria for the study participants are women and adolescent girls with disabilities (intervention and control groups) and male counterparts (intervention group). The exclusion criteria for this study are women and adolescent girls with mental and intellectual disabilities. Engaging male peers in menstrual hygiene management is the key intervention in the study. No blinding or randomization will be applied. The expected primary outcome in the intervention group will be an improvement in the menstrual hygiene management of women and adolescent girls with disabilities in the selected sub-districts of Bangladesh. Two times data will be collected from the intervention and control groups using the ‘Menstrual Practice Needs Scale-36’, ‘Perceived Stress Scale’, and ‘Multi-dimensional Scale of Perceived Social Support’. The analysis of variance (ANOVA) test will be applied to a two-point data series to assess statistical significance.

Results

The result of the study will be published in a scientific journal. The outcomes of the research will be disseminated to local policymakers and health planners. The health administrator will get evidence-based information on gender-inclusive menstrual hygiene management for women and adolescent girls with disabilities through study result dissemination events.

Conclusion

This protocol for a quasi-experimental study in Bangladesh highlights the potential advantages of involving male peers in the menstrual hygiene management of women and adolescent girls with disabilities. It may promote gender-inclusive behavior in selected subdistricts of Bangladesh.

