## Introduction

Menstrual hygiene management (MHM) is a critical aspect of women and adolescent girls' health and well-being, yet it remains a largely neglected issue, especially among women and girls with disabilities [1]. The absence of proper MHM can lead to a range of health problems and social stigma, affecting not only physical health but also emotional and psychological well-being [2]. In Bangladesh, as in many other low- and middle-income countries, women and girls with disabilities often face compounded challenges related to menstruation due to a lack of accessible facilities, appropriate information, and social taboos surrounding the topic [3]. Addressing these challenges requires a multifaceted approach that includes raising awareness, improving access to resources, and fostering community support.

Bangladesh, with a population of approximately 165 million, is home to 7.9% of people aged more than 15 years who suffer from functional difficulties [4]. The country has made strides in promoting gender equality and women's empowerment, but many women and girls with disabilities continue to face barriers that limit their access to essential services and education, including menstrual hygiene management [3].

Recognizing the need to address these issues, the study "Effects of Involvement of Male Counterparts in Menstrual Hygiene Management of Women and Adolescent Girls with Disabilities in Selected Sub-districts of Bangladesh" was conceived. This research aims to investigate the impact of involving male counterparts, such as fathers, brothers, and husbands, in MHM practices to improve the overall well-being of women and adolescent girls with disabilities in selected sub-districts of Bangladesh.

This is the first intervention study where male peers will be involved in the menstrual hygiene management of women and adolescent girls with disabilities. The rationale behind involving male counterparts in MHM is multifaceted. Historically, discussions and interventions related to menstrual hygiene have primarily been directed toward women and girls themselves, often excluding men from the conversation. However, men play a crucial role in shaping the perceptions and practices surrounding menstruation within the household and community [5]. By engaging male counterparts in MHM, this study seeks to challenge social norms and promote a more inclusive and supportive environment for women and girls with disabilities.

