## Materials and methods

Design and setting

This is a quasi-experimental study. There will be one intervention group and one control group. The groups can be considered parallel groups. The participant allocation ratio (intervention: control) will be 1:1. The study will be conducted in the selected sub-districts of Bangladesh - Bogura Sadar and Chapai-Nawabganj Sadar. Bogra Sadar is an upazila of Bogra District in the Division of Rajshahi, Bangladesh. Nawabganj Sadar is an upazila of Nawabganj District in the Division of Rajshahi, Bangladesh. There are 64 districts and eight divisions in Bangladesh [6]. The study sites have been selected purposefully, considering sociocultural factors such as the fact that both study sites are agriculture-based societies. Both are disaster-prone areas of Bangladesh and both are semi-urban in nature. These criteria are in line with the study's purpose.

Study population

Inclusion and Exclusion Criteria

Inclusion criteria: Women and adolescent girls with disabilities who fulfill the following inclusion criteria - the age range for adolescent girls with disabilities: 10 to <18 years; the age range for women with disabilities: 18 to 45 years; the women and adolescent girls with disabilities are menstruating women and adolescent girls; women and adolescent girls with physical or hearing or visual or combined disability; and duration of stay at the study site: more than or equal to six months. Inclusion criteria for the male counterparts - relationship status with the female participant, i.e., husband, father, or elder brother; age limit: 18-65 years; and duration of stay at the study site: more than or equal to six months.

Exclusion criteria: Women and adolescent girls who meet the following exclusion criteria as well as their male counterparts will be excluded from this study: persons who are presently pregnant, have any mental and intellectual disabilities, have a terminal illness, and all those unable to provide informed consent.

Sample Size

We calculated the sample size using the G Power software (version 3.1.9.4) [7]. The software has been developed by Axel Buchner, who is associated with Heinrich Heine University Düsseldorf, a public university in North Rhine-Westphalia, Germany, founded in 1965 [8]. Analysis of variance for repeated measures within-between interactions assumed a medium Cohen's effect size of 0.13 [9].

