Bangladesh has a patriarchal society that is dominated by men [10]. The topic of menstruation is taboo in society [11]. During follow-up, there is a substantial risk of participant loss, particularly for the male counterparts. When taken into account in the socio-cultural context, those lost to follow-up are regarded as 30%. Considering the lost-to-follow-up rate, a total of 156 (78 - intervention and 78 - control) women and adolescent girls with disabilities were recruited in the study.

Recruitment Process

Two community health workers have been recruited for the study from the 'Organization of People with Disabilities'. The lead investigator provided them with training and supportive supervision. 'Organization of People with Disabilities' is a root-level organization that especially works for people with disabilities at the community level. The recruited community health workers will meet with community members door-to-door. They will use "Washington Group Short Set Questionnaires on Functioning” for disability screening. The questionnaire set has questions on visual, hearing, walking, concentration, communication ability, and self-care [12]. It is a disability identification tool using which it is possible to identify those who are at risk of disability. From the positively screened individuals with disabilities, study participants will be recruited. Male counterparts’ involvement will be considered a critical intervention in the study. In the intervention group, male counterparts (father, husband, and brother) of the women and adolescent girls with disabilities will also be included as study participants. The study will consider these male peers' involvement and participation in managing menstrual hygiene as the key interventions. The study will run from April 2022 to March 2025.

Interventions

Figure 1 shows the procedure of the study. The intervention group will receive 10 months of health education on menstrual hygiene management as well as the role of male counterparts in managing menstrual health and hygiene. Blinding will not be used in this study. Community health workers will visit the study participants on a door-to-door basis. They will provide health education information in one-on-one meetings and courtyard sessions.

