## Discussion

Women and adolescents with disabilities face many types of challenges. Challenges during their menstruation days are some of the worst challenges they have to face [23]. They have to rely on family members to different extents based on their disability types and severity [24]. They face difficulty in getting menstrual products and treatment during menstruation if male peers are unaware of menstrual needs [25,26].

In many low- and middle-income countries (LMICs), men are the primary decision-makers [27]. It is important to engage male counterparts in the sexual and reproductive healthcare issues of female peers. It is evidenced in different studies that their involvement created positive outcomes. In developing nations, male involvement can lead to better maternal health outcomes, according to a systematic review and meta-analysis by Yargawa et al. [28]. A study conducted by Atwine et al. in 2017 found that male involvement was associated with the normal nutritional status of under-five children in Uganda [29]. Another study conducted by Yemata et al. in 2023 found that husband participation in birth preparedness and complication readiness was beneficial for pregnant mothers [30].

There are significant practical ramifications to the quasi-experimental study investigating the participation of male counterparts in the management of menstruation hygiene for women and adolescent girls with disabilities. These results can guide the creation of programs and regulations meant to promote an environment that is more welcoming and encouraging, especially for women and adolescent girls with disabilities. The study's inclusion of male partners may aid in eradicating stigmas associated with menstruation and advancing gender equality. Culturally, males are not only breadwinners but also act as protective shields for their female counterparts in Bangladesh. When men are well informed and take part in MHM, their involvement will provide a protective shield against negative attitudes toward their female counterparts. In turn, these can enhance the general well-being of women and girls with disabilities by giving them access to the tools and emotional support they need during their menstrual cycles. In conclusion, this study emphasizes the importance of identifying and meeting the particular needs of this group of people, which will ultimately lead to improved menstrual hygiene management and increased gender justice.

Strengths and limitations

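### An eligible, consenting male counterpart is enrolled only in the intervention group and control women are not screened for one, so the groups can differ on a factor the protocol treats as a determinant of the outcome

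*Protocol article*

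**What the plan says.** The Abstract (Methods) states eligibility by group: "women and adolescent girls with disabilities (intervention and control groups) and male counterparts (intervention group"). Recruitment Process, under Materials and methods, repeats the split: "In the intervention group, male counterparts (father, husband, and brother) of the women and adolescent girls with disabilities will also be included as study participants".

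Inclusion and Exclusion Criteria defines the man: "relationship status with the female participant, i.e., husband, father, or elder brother; age limit: 18-65 years", with at least six months' residence at the site. The exclusion sentence covers male counterparts as well as the women, and ends with those who "have a terminal illness, and all those unable to provide informed consent".

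The woman's own criteria are age, menstruating status, disability type and residence: "women and adolescent girls with physical or hearing or visual or combined disability; and duration of stay at the study site". None concerns having a male counterpart, in either group. The article describes no step that identifies counterparts of control women.

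On the role of the men, Recruitment Process says: "The study will consider these male peers' involvement and participation in managing menstrual hygiene as the key interventions".

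**The concern.** The man's presence and agreement are built into one group and left open in the other. The protocol itself treats men as part of the causal pathway. The Introduction says that "men play a crucial role in shaping the perceptions and practices surrounding menstruation within the household and community", and the Discussion says of the women that "They face difficulty in getting menstrual products and treatment during menstruation if male peers are unaware of menstrual needs". One outcome instrument, the social support scale, has family and significant-other subscales. The Sample Size section calls menstruation taboo, so a man who agrees to join may not be typical.

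There is no randomisation to balance this. The Data Analysis Plan promises adjustment for potential confounders, but it cannot adjust for something that was never recorded in controls. At stake is whether a difference between groups reflects the education programme or the kind of household each group was drawn from.

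**Working it through.** **1. Eligibility side by side**

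| | Intervention | Control |
|---|---|---|
| Woman: age, menstruating, disability type, residence | yes | yes |
| Man enrolled as participant | yes | no |
| Man is husband, father or elder brother, 18-65, resident at least six months | applies to the enrolled man | not asked |
| Man able to consent | applies to the enrolled man | not asked |

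No sentence excludes an intervention-group woman who lacks such a man. If she were enrolled anyway, she could not receive the key intervention. Either the group is selected on having a man, or part of it goes without the treatment under study. The article does not say which.

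**2. The plan's own sample size, to set a scale**

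Stated: effect size 0.13, within-between interaction, two time points, 120 women (60 per group). Not stated, so assumed: two-sided alpha 0.05, power 0.80, pre-post correlation ρ = 0.5, and 0.13 entered as f.

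- λ = f² × N × m / (1 − ρ) = 0.0169 × 120 × 2 / 0.5 = 8.11. With 1 and 118 degrees of freedom the power is 0.806, so 120 is reproduced.
- The same test expressed as a t-test on change has λ = δ² × N/4, so δ = √(8 × f² / (1 − ρ)) = √(8 × 0.0169 / 0.5) = 0.52 SD of change.
- δ depends on ρ: it is 0.44 SD at ρ = 0.3 and 0.67 SD at ρ = 0.7. The 0.52 SD is therefore a working value, not a figure in the article.

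**3. What cancels and what does not**

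Let q be the share of controls with no eligible, willing man. Let g be the amount, in SD of change, by which such women would change less over the 10 months than other untreated women. If the intervention group contains no such women:

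- a constant difference in level drops out of the before-after comparison;
- a difference in change does not, and bias = q × g.

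**4. Illustration (q and g both assumed)**

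Two-sample t-test on change, 60 per group, no true effect, noncentrality = bias × √(60/2).

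| q | g (SD) | Bias (SD) | Bias / 0.52 | False-positive rate |
|---|---|---|---|---|
| any | 0 | 0 | 0% | 5.0% |
| 0.1 | 0.2 | 0.02 | 4% | 5.1% |
| 0.2 | 0.2 | 0.04 | 8% | 5.5% |
| 0.2 | 0.5 | 0.10 | 19% | 8.4% |
| 0.3 | 0.5 | 0.15 | 29% | 12.9% |
| 0.4 | 0.5 | 0.20 | 38% | 19.2% |
| 0.5 | 0.5 | 0.25 | 48% | 27.4% |

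The upper rows are negligible and the lower rows are not. The documents do not show which row applies.

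**5. Attrition**

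The Sample Size section allows for 30% loss and expects it particularly among male counterparts, who exist as participants in one group only. If a woman's follow-up ends when her man leaves, loss depends on household support in one group and not in the other. The documents give no figure from which to size this.

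**The case against.** Several points on the other side stand.

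- **The requirement is inferred.** The women's criteria do not mention a man, and a condensed article may leave the screening of controls to the full protocol. This limits the certainty. It does not remove the split in enrolment, which is stated twice.
- **Widows and women with absent husbands.** A reader might infer that they are barred from the intervention group. They are not: a father or elder brother also qualifies. Only women with none of the three eligible and willing are affected.
- **Levels cancel.** A willing man may go with better support and lower stress at baseline, but outcomes are measured before and after in both groups. Only different change or different attrition matters, and the article gives no evidence that untreated women with and without such a man diverge over 10 months. If g = 0, there is no bias by this route.
- **Direction.** A reader might infer that all three scales are biased towards benefit. The documents do not support this. Better-supported women may start nearer the top of the menstrual practice scale, where 3 means no unmet need, and have less room to improve. That would pull towards no effect.
- **Size.** A g of 0.5 SD without any intervention is almost the whole 0.52 SD, so it is a high value.
- **Partly acknowledged.** The article plans confounder adjustment and admits residual confounding. Both statements are general. Neither names this factor or provides for recording it in controls.

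**Conclusion.** The point holds as a design weakness of unknown size and direction. Men are enrolled in the intervention group only, control women are not screened for an eligible man, and the protocol treats men as a determinant of menstrual management. Without randomisation, this can bias the group-by-time comparison through different change or attrition.

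The range of 0-0.25 SD, with a false-positive rate of 5% to about 27%, is an illustration. It rests on assumed q (0.1-0.5), assumed g (0-0.5 SD) and 60 per group analysed. The comparison with 0.52 SD also assumes a pre-post correlation of 0.5. The documents do not support a claim that the result is biased by a known amount, or necessarily in favour of the intervention. They do support saying that the plan as written could neither detect nor adjust for the imbalance, and that this is cheap to repair.

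**What to change.** - State one counterpart-availability criterion for women in both groups: a husband, father or elder brother who meets the age and residence limits already set for the men. Say what happens to an intervention-group woman who has none.
- The article reports the 156 women as already recruited. For them, record counterpart availability and relationship type in both groups, and name both variables in the confounder adjustment.
- Report a sensitivity analysis restricted to women with an eligible counterpart in both groups.
- If control women or their men are asked about willingness, use the answer only in a further sensitivity analysis. It should not define the primary set: a hypothetical answer on a taboo topic, with nothing offered, is not the same as actual consent at enrolment.

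**Cost.** A few extra questionnaire items. Data are collected only at baseline and after 10 months, so for recruited controls the next contact may be the final interview, and late answers are an imperfect match. The restricted analysis loses precision: if 20-40% of controls drop out of it (60 to 48 or 36, against 60 treated), power at the assumed 0.52 SD falls from 0.81 to about 0.76 or 0.68.

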## Introduction

Menstrual hygiene management (MHM) is a critical aspect of women and adolescent girls' health and well-being, yet it remains a largely neglected issue, especially among women and girls with disabilities [1]. The absence of proper MHM can lead to a range of health problems and social stigma, affecting not only physical health but also emotional and psychological well-being [2]. In Bangladesh, as in many other low- and middle-income countries, women and girls with disabilities often face compounded challenges related to menstruation due to a lack of accessible facilities, appropriate information, and social taboos surrounding the topic [3]. Addressing these challenges requires a multifaceted approach that includes raising awareness, improving access to resources, and fostering community support.

Bangladesh, with a population of approximately 165 million, is home to 7.9% of people aged more than 15 years who suffer from functional difficulties [4]. The country has made strides in promoting gender equality and women's empowerment, but many women and girls with disabilities continue to face barriers that limit their access to essential services and education, including menstrual hygiene management [3].

Recognizing the need to address these issues, the study "Effects of Involvement of Male Counterparts in Menstrual Hygiene Management of Women and Adolescent Girls with Disabilities in Selected Sub-districts of Bangladesh" was conceived. This research aims to investigate the impact of involving male counterparts, such as fathers, brothers, and husbands, in MHM practices to improve the overall well-being of women and adolescent girls with disabilities in selected sub-districts of Bangladesh.

This is the first intervention study where male peers will be involved in the menstrual hygiene management of women and adolescent girls with disabilities. The rationale behind involving male counterparts in MHM is multifaceted. Historically, discussions and interventions related to menstrual hygiene have primarily been directed toward women and girls themselves, often excluding men from the conversation. However, men play a crucial role in shaping the perceptions and practices surrounding menstruation within the household and community [5]. By engaging male counterparts in MHM, this study seeks to challenge social norms and promote a more inclusive and supportive environment for women and girls with disabilities.

The research employs a quasi-experimental design to assess the effectiveness of this intervention. It will involve the implementation of educational programs and courtyard sessions that target both male and female family members of women and adolescent girls with disabilities in the intervention group. The study will also evaluate changes in menstrual practice needs, perceived stress, and perceived social support of women and girls with disabilities.

The findings of this study are expected to contribute significantly to the body of knowledge surrounding menstrual hygiene management, particularly in the context of women and girls with disabilities in Bangladesh. It is hoped that the research will shed light on the potential benefits of involving male counterparts in MHM and inform future policies and programs aimed at improving menstrual health and overall quality of life for this vulnerable population. Furthermore, the study's insights may have broader implications for addressing gender-based disparities and promoting inclusive practices in similar settings globally, emphasizing the importance of collaboration and shared responsibility in achieving gender equity and social justice.

